# The effects of psychosocial stimulation on the development, growth, and treatment outcome of children with severe acute malnutrition age 6–59 months in southern Ethiopia: a parallel group cluster randomized control trial (EPSoSAMC study)

**DOI:** 10.1186/s12889-019-7916-5

**Published:** 2019-12-02

**Keywords:** Cluster randomized trial, Psychosocial stimulation, Under-five children, Severe acute malnutrition, Ethiopia

## Abstract

**Background:**

Severe Acute Malnutrition (SAM) remains a major cause of child mortality. To improve the management and survival of children the World Health Organization (WHO) endorsed the protocol for the management of SAM. The protocol suggested the integration of psychosocial stimulation as part of the medico-nutritional care process to prevent the long-term adverse developmental impact of the SAM. However, there is little scientific evidence behind the recommended stimulation intervention.

**Method:**

A parallel-group cluster-randomized controlled trial will be conducted among 144 children with SAM age 6–59 months in Southern Ethiopia. The study will have two groups where: children with SAM admitted in the intervention health facilities will receive psychosocial stimulation in addition to the routine inpatient care and for 6 months after discharge. Children with SAM admitted in the SC of the control health facilities will receive the routine inpatient care without psychosocial stimulation and home-based follow up for 6 months after discharge. All mothers/ caregivers will also receive uniform health education on child health-related issues. The primary outcome of the study will be child development while the secondary outcomes will include child growth and treatment outcome. All outcomes will be assessed four times: at enrollment, upon discharge from the SC, at 3 and 6 months of follow up. The data will be analyzed using STATA Version 15 Statistical Software. The anthropometric Z-scores and percentile of the median will be calculated child using WHO Anthro Version 3.2.2 Statistical Software. To assess the overall effect of the intervention by controlling other potential contributing factors, a generalized linear mixed model will be used.

**Discussion:**

The present study will have an important contribution in generating supplementary evidence regarding the effect of psychosocial stimulation interventions on the development and growth outcomes of children with SAM. The study will further address the impact of the intervention on treatment outcome indicators that are still under-researched areas requiring new scientific evidence.

## Background of the study

Globally approximately 151 million (22%) children under 5 years of age suffer from stunting and nearly 51 million (7.5%) were wasted in 2017. More than one-third of all stunted and more than one-quarter of all wasted children under 5 years of age are living in Africa [1]. According to the Ethiopian Demographic and Health Survey (EDHS) report, the prevalence of stunting, wasting and underweight among children under 5 years of age was 38, 10 and 24% respectively [2].

In view of the fact that malnutrition remains a direct or indirect cause of child mortality, the WHO developed the standard protocol to improve its management process and the survival of children. Considering the benefits of early child development programs in improving the long term developmental potential of children suffering from undernutrition, the protocols suggested the inclusion of emotional and physical stimulation through play programs during rehabilitation and after discharge [3]. However, few studies were conducted globally to examine the effect of the stimulation interventions provided in conjunction with the routine medico-nutritional care of children with SAM admitted in the nutrition rehabilitation unit. The study conducted in Bangladesh found out that the inclusion of the psychosocial stimulation interventions with the routine medico-nutritional care improved the mental development, motor development, weight-for-age Z-score and no change was noted for children behavior [4]. In Jamaica, the stimulation program showed a significant impact on the mental development of severely malnourished children [5]. In Ethiopia, the only study conducted among children with SAM admitted in the Stabilization Center (SC) of Jimma University Hospital revealed that the intervention significantly improved the gross motor functions during their hospital stay and fine motor functions with only small effect size after discharge from the hospital. However, it did not contribute significantly to linear growth and nutritional outcomes [6].

The reviewed studies have certain methodological issues that lead to very low-quality findings across important outcome indicators. A few of the limitations include the introduction of information contamination [6], the high level of lost to follow up (4,5&6), the lack of randomization [4].and unequal observation between the intervention groups [4]. Furthermore, in all of the reviewed studies, the full WHO recommendations on psychosocial stimulation [3, 7] were not implemented.

One of the goals of introducing stimulation and support intervention is to promote growth during the rehabilitation phase and to improve the treatment of severely malnourished children [8].

The reviewed studies did not adequately address the impact of the intervention on important treatment outcome indicators such as weight gain, duration of treatment, and the number of children discharged after recovery and the recurrence rate of malnutrition after discharge from the SC. Although positive findings have been observed from the few studies conducted in the area and the promotion of the stimulation intervention by organizations such as the WHO, the finding of a recent systematic review clearly indicated the need for further scientific evidence behind the inclusion of the stimulation intervention in the routine management of children with SAM [9].

## Hypothesis and objectives of the study

### Hypothesis

It is hypothesized that children with SAM age 6–59 months admitted in the SC who receive psychosocial stimulation interventions with the routine inpatient care and for 6 months after discharge will have a significantly greater improvement on their development, growth and treatment outcomes compared to those who receive the routine care alone.

### Primary objective

To examine the effect of psychosocial stimulation interventions provided with the routine inpatient care and for 6 months after discharge on the development, growth and treatment outcome of children with SAM age 6–59 months in Southern Ethiopia.

### Secondary objectives

To determine the effect of psychosocial stimulation interventions provided with the routine inpatient care and for 6 months after discharge on the development of children with SAM age 6–59 monthsTo determine the effect of psychosocial stimulation interventions provided with the routine inpatient care and for 6 months after discharge on the growth of children with SAM age 6–59 monthsTo determine the effect of psychosocial stimulation interventions provided with the routine inpatient care and for 6 months after discharge on the treatment outcome of children with SAM age 6–59 months

## Research methods and materials

### Study area and design

The study will be conducted in Silti Zone, Southern Regional State of Ethiopia. Administratively Silti Zone comprises nine District/Woredas with the one administrative town namely: Worabe that is located 175 km from Addis Ababa. In 2017, the total population of the Silti Zone was estimated to be 937,212 of which 482,527 were females and 454,685 were males. Nearly 837,207 (90%) of the total population lives in rural areas [10]. According to the report of the Zonal Health Office, there are thirty-five health facilities providing preventive and curative health services for their respective populations. Among these health facilities, nineteen of them have been providing inpatient care for children with SAM based on the national protocol for the inpatient management of SAM in their dedicated SC. The study will include 18 health facilities that have a dedicated SC. A Parallel-Group Cluster-Randomized Controlled Trial (RCT) will be used. The design is adopted because of its logistical feasibility for the study considering the difficulties to manage the use of different interventions for children admitted with similar cases in single SC. Furthermore, from our empirical observation mothers/ caregivers of children with SAM admitted in the SC usually create intimate living arrangements and relationships with each other possibly due to their extended stay in the SC of the health facility. They usually chat, prepare, and eat their food together. The intervention will further promote their intimacy since it has a daily informal group play session involving mothers/ caregivers and their children. If individual randomization is used within each health facility, the potential information contamination between the two groups could lead to the adoption of the psychosocial stimulation intervention by the control group, which will reduce the likelihood of finding substantial differences between the two groups of the study. The design is also appropriate considering the ethical issues that will be raised in relation to withholding intervention from some children and not others in the same SC of the health facility. The study protocol is prepared based on the SPIRIT guidelines and included all the recommended items of a clinical trial protocol (Fig. 1).

**Fig. 1 Fig1:**
[figure not shown]
Flow Diagram for the Trial of Psychosocial Stimulation Intervention for children with SAM Age 6–59 Months, Southern Ethiopia, 2019

### Eligibility criteria for health facilities/clusters

All public health facilities in the study areas having a dedicated SC for the inpatient care of children with SAM and are willing to participate in the study will be eligible to take part in the study. At the time of submission, the Zonal Health office that has been managing all the health facilities agreed on the conduct of the study on behalf of the health facilities.

One health facility was excluded since it has recently established the SC and started providing inpatient care for children with SAM, unlike others.

### Eligibility criteria for children

During the recruitment period, all children with SAM age 6–59 months who will be showed up to the SC of selected health facilities for the inpatient care and fulfill the admission criteria of the Ethiopian guidelines for the management of acute malnutrition will be eligible study subjects. As per protocol, SAM in children age 6–59 months is diagnosed when; Weight–for-Length/Height (WFL/H) less than 70% of the WHO reference median or less than – 3 Z score and/or the presence of bilateral pitting edema and/or Mid Upper Arm Circumference (MUAC) < 11.5 cm. The inpatient admission criteria for children include having diagnosed with SAM and the presence of any of the medical complications listed in the national protocol or failed appetite tests or having diagnosed with SAM and referred from Outpatient Therapeutic Program (OTP) [11].

The inclusion criteria in the selection of eligible children with SAM;
Children age 6–59 months with the diagnosis of SAM fulfilling the inpatient admission criteria based on the Ethiopian guidelines for the management of acute malnutritionThe mother/ caregiver of the child has a plan to stay in the study area for at least 6 months after the discharge of her children from the SCThe mother/ caregiver of the child agrees for the inpatient care of SAM during Phase 2 treatment in the SCThe mother/ caregiver of the child agrees to present in the SC during the inpatient care

The exclusion criteria in the selection of eligible children with SAM;
Children with the diagnosis of other chronic medical conditions such as tuberculosis and HIV/AIDS that could be identified by the health workers during admission or laterChildren with clinically apparent congenital abnormalities, obvious disabilities and sensory impairments (hearing and visual problems) that could affect outcome measurements and those children with twin birthFamilies of children living far from the health facilities included in the study

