### Personnel for the study

Health workers who will be recruited from the SC of each of the health facilities will take the responsibility for the recruitment; follow up of children during the SC admission period, for supporting the intervention workers/play guides and for the collection of enrollment and other data. Depending on the caseload in the SC of the health facility, one or two health workers will be included in the study team from each of the health facilities.

For each of the health facilities, one young female intervention worker/ play guide who have completed at least grade 10 will be recruited from the local community considering their child-friendliness. In the intervention health facilities, the intervention workers/ play guides will assume the responsibility of facilitating the stimulation intervention during the inpatient care and for the period of 6 months after discharge through a home visit. They will also provide health education, conduct home-based follow up, collect follow up data, participate in the preparation of suitable toys from locally available materials, help mothers/ caregivers and other family members, and equip them with the essential skills for the implementation of the intervention. For each of the control health facilities, the intervention worker will only be responsible for providing health education, conducting home-based follow-up, and collection follow-up data. A separate mobile team of testers/ outcome assessors will be recruited considering their academic background and previous experience to collect anthropometric data and administer developmental tests. They will be unaware (Blind) to the allocation status of the children and the health facilities to avoid measurement bias.

Experienced supervisors will be recruited to oversee the activities of the health workers, the team of testers/ outcome assessors and the intervention workers. The field-level project coordinator under the direct guidance of the principal investigator will be responsible for the overall coordination and follow up.

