### Training of the study team

Intensive training will be given for the study personnel by a team of senior trainers. Separate training will be provided for each of the study teams considering the allocation status of their health facilities, their role in the study and their professional experience. For the intervention health facilities, health workers will be trained on the basis of psychosocial stimulation and the study procedures including recruitment and data collection procedures, facilitation of psychosocial stimulation, and facility-level follow up procedures. The training of the intervention workers/play guides will focus on the basics of childcare, child growth, and development, about the communication methods and other intervention-related issues such as the study procedures, the facilitation of the stimulation intervention and follow up procedures. For the control health facilities, the training of both the health workers and intervention workers/ play guides will not include the stimulation intervention related topics. The measurement team will also be trained on the standards of anthropometric measurement and administration of development tests. In all the training sessions, the trainees will go out to the field to practice the practical components of the training.

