### Recruitment procedure

Prior to the recruitment, a dedicated play corner will be established at each of the intervention health facilities and equipped with all the essential materials including age and developmentally appropriate play materials that will be used for providing stimulation intervention through play program. Intensive efforts will be undertaken to make the atmosphere in the SC room and the play corner relaxed, cheerful and welcoming.

In the 2 months recruitment period, health workers will screen children with SAM who will be shown up to the SC of the selected health facilities and recruit the first eight children with their mothers/ caregivers based on the study inclusion criteria. The health workers will discuss with the caretakers of all children fulfilling the inclusion criteria about the basic concepts of child nutrition, child growth and development and the details of the study including the involvement of the mothers/caregivers, the associated training need, about the required measurements and follow up procedures. Then, they will invite mothers/ caregivers to participate in the study with their child. After having received written informed consent from the mothers/ caregivers for their voluntary participation with their child, they will collect enrollment data.

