### The intervention and follow-up

The intervention and follow up of the study subjects will take place for 8 months. In the intervention health facilities: children with SAM age 6–59 months will receive psychosocial stimulation in addition to the routine inpatient care in the SC and for 6 months after discharge through home-based follow up. In this study, the full WHO recommendations on emotional and physical stimulation [3, 7] will be implemented in the intervention health facilities. After the initial phase of treatment (Phase-I), children with SAM will participate in the psychosocial stimulation intervention at the regular schedule during the transition and phase 2 of the inpatient care and for 6 months after discharge through home-based follow up. In the SC, the child will spend prolonged periods on large play mats with other children, mothers and/or an intervention worker/ play guide on a daily basis to facilitate informal group play sessions. Each of the mother/ caregiver and their child will also participate in a half-hour of individual play sessions on a daily basis with an intervention worker/ play guide worker. Since, an average of 2–3 weeks are required to offer the full inpatient care (Phase 1, Transition Phase and Phase 2) in the SC, each child will receive about 12–19 individualized stimulation sessions in the SC after Phase 1 medico nutritional care. The play activities and toys will be selected to develop both motor and language skills considering the age and the level of child development. Accordingly, each play session will include language activities, motor activities, and activities with toys.

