### Data management and analysis

Two independent data entry operators will check, code, and enter the collected data into Epi Info Version 7 Statistical Software. STATA Version 15 Statistical Software will be used for the statistical analyses. The anthropometric Z-scores and percentile of the median will be calculated using the WHO Anthro Version 3.2.2 Statistical Software. Proportions, percentages, measures of central tendency together with measures of dispersion will be used to summarize the collected data. For each test item in the developmental measures, a binary outcome variable with the categorical score of a pass or fail will be created where; pass will be considered for items that the child will be tested and passed while fail will be considered for items that the child will be tested and failed or refused. No opportunity to perform will be considered for items that the child will not be tested for due to various reasons including medical conditions, which will be treated as missing values. A numerical score will be computed by adding up the points of all items for each of the developmental dimensions. For the social-emotional dimensions of the child development that will be measured using ASQ: SE, a numerical score will be computed by adding up the points of all items on the questionnaire. From the anthropometric data of weight, height, and MUAC, the nutritional status of children will be determined. The proportion of cases in either group of the study that will be recovered, defaulted, and dead or relapsed within the study period will be also calculated and reported.

In a cluster RCT, participants within the same cluster may be more similar than those in different clusters, which may lead to the correlation of observations within the clusters. Failure to account this in the analysis and the subsequent use of standard statistical methods will make the resulting standard error of the intervention effect too small, along with the confidence interval and *P*-value [22]. In all the analyses that will be conducted using the data of all randomized study subjects, the clustering nature of the data will be considered. In order to assess the overall effect of the intervention by controlling other potential contributing factors, a Generalized Linear Mixed Model (GLMM) that is flexible to address the outcome variables to be measured in this study will be used.

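### The chronic-disease exclusion has no cut-off and, as worded, lets staff who know the arm exclude a child after baseline and after exposure

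*Protocol article*

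**What the plan says.** In the Protocol article, under Eligibility criteria for children, the first exclusion is "Children with the diagnosis of other chronic medical conditions such as tuberculosis and HIV/AIDS", qualified as conditions that "could be identified by the health workers during admission or laterChildren with clinically apparent congenital abnormalities". The rule ends at 'later'. The words that follow open the next item, and the missing break comes from text extraction. The list is introduced as criteria for selecting eligible children. No date or treatment phase closes the rule, and the conditions are given only as examples.

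Data management and analysis names the analysis set in one clause: "In all the analyses that will be conducted using the data of all randomized study subjects", clustering will be taken into account.

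The people who apply the exclusion are facility staff. Personnel for the study says: "Health workers who will be recruited from the SC of each of the health facilities will take the responsibility for the recruitment". The same workers follow the children during the inpatient stay and support the play guides. Training of the study team says: "Separate training will be provided for each of the study teams considering the allocation status of their health facilities". Recruitment procedure says: "Prior to the recruitment, a dedicated play corner will be established at each of the intervention health facilities". Only the mobile testers are described as blind: "They will be unaware (Blind) to the allocation status of the children and the health facilities to avoid measurement bias".

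On timing, Outcome measurement and tools places baseline at the transfer from Phase I to the Transition Phase. The intervention and follow-up says: "After the initial phase of treatment (Phase-I), children with SAM will participate in the psychosocial stimulation intervention", and this continues for 6 months after discharge.

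**The concern.** An eligibility rule should close before follow-up starts. This one does not. Followed literally, it allows a child to be consented, measured at baseline, given stimulation and then declared ineligible when a chronic illness is recognised.

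Two features make that matter. The people who recognise the illness know which arm the facility is in. Also, a search for tuberculosis or HIV may plausibly be prompted by poor weight gain, non-response or relapse, all of which the Secondary outcome section lists as outcomes. Removal would then depend partly on outcome. If it happened more in one arm, the remaining children would no longer be comparable: removing more poorly performing children from the intervention arm would flatter the intervention, and removing more from the control arm would hide an effect.

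Each cluster has only eight children, so one removal is 1/8 = 12.5% of a cluster.

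**Working it through.** **Timing.** The order of events is admission, Phase I, baseline at transfer to the Transition Phase, stimulation in the Transition Phase and Phase 2, discharge, then 6 months at home. A diagnosis during Phase I is later than admission but before baseline and exposure, so excluding that child does no harm to the comparison. A diagnosis in the Transition Phase, Phase 2 or follow-up comes after baseline and exposure. The wording covers both cases. Clusters rather than children are randomized, so the analysis clause is best read as all enrolled children in randomized clusters. A child removed in the second case cannot also be in that set.

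**The plan's own figures.** Inputs from Sample size determination and sampling technique: mean 15.8, SD 4.4, 10% improvement (0.10 × 15.8 = 1.58 points), t = 4 measurements, r = 0.02, alpha 0.05, power 90%, ICC 0.05, k = 9 clusters per arm, 20% for dropout.

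- Individual randomization, two-sided: n = 2·SD²·(z₀.₉₇₅ + z₀.₉₀)²·[1 + (t − 1)r] / (t·d²) = 162.97 × 1.06 / 4 = 43.19, rounded up to 44 (stated: 44).
- Fixed number of clusters: n·k·(1 − ρ)/(k − nρ) = 44 × 9 × 0.95 / (9 − 2.2) = 55.3, rounded up to 56.
- Dropout: 56 × 1.2 = 67.2, rounded up to 68 (stated: 68).
- Per cluster: 68/9 = 7.6, rounded up to 8, giving 72 per arm and 144 in total (as stated).

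These figures reproduce, and the point does not change them.

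**Possible shift in the fine motor difference.** The document gives no rate of late diagnosis and no deficit in affected children, so both are assumed. Let 15% of enrolled children be affected and score D SDs lower than the rest, and let a fraction x of the arm, all of them affected, be removed. The mean of those left, relative to unaffected children, is −D × 4.4 × (0.15 − x)/(1 − x).

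- x = 0: (0.15)/(1) = 0.1500
- x = 0.05: (0.10)/(0.95) = 0.1053
- x = 0.10: (0.05)/(0.90) = 0.0556

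| Removal, one arm vs other | D = 0.5 | D = 1.0 |
|---|---|---|
| 5% vs 5% | 0 | 0 |
| 10% vs 5% | 0.11 points (7% of 1.58) | 0.22 points (14%) |
| 10% vs 0% | 0.21 points (13%) | 0.42 points (26%) |

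**A recovery example, one-sided by construction.** Suppose 58 of 72 children recover in each arm (58/72 = 80.6%) and three non-responders in one arm only are excluded late. That arm then shows 58/69 = 84.1%, with no true effect.

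**Power.** After 20% dropout, 72 × 0.8 = 57.6 children per arm remain, and power under the plan's assumptions is 0.913. Late removal of a further 5%, 10% or 15% in both arms leaves 54.7, 51.8 or 49.0 per arm, with power 0.903, 0.891 or 0.877. The loss of power is small; any harm would come from selection.

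**The case against.** The strongest reply is that this is a selection rule and nothing more. It stands under a heading about selecting eligible children, and Phase I gives 'later' a natural meaning before baseline. No sentence tells a site to withdraw an enrolled child, stop follow-up or delete data. On that reading the eligibility section governs entry, the analysis section governs the analysis set, and the two agree. This stands as a possible intention. It does not remove the problem, because the text sets no limit and 18 facilities may read it differently.

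A related reply is that an article may leave the handling of late-found ineligibility to a fuller document. That is true of the handling, and its absence is not criticised here. The open-ended rule, however, is stated in the article itself.

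A reader might also infer that late cases would be found more often in the intervention arm because of the daily play sessions. The document does not support this as a fact. The extra contact is mainly with the play guide, whereas the rule names the health workers, who care for inpatients in both arms. The same five home visits are scheduled in both arms, and the 3- and 6-month measurements are made in both by blinded testers. Unequal detection remains possible, since those who identify the illness are unblinded and the list of conditions is open, but it is an inference.

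**Conclusion.** The point holds as a defect of wording with a possible consequence for validity. The exclusion has no end point, is applied by staff who know the arm, and as written permits removal after baseline and exposure. Such removal would conflict with analysing all randomized subjects.

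Two stronger conclusions are tempting and should not be drawn. The document does not contain a demonstrated contradiction, because the Phase I reading reconciles the passages. Nor does it show bias, because nothing in it indicates that late diagnoses would follow poor response or differ by arm.

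The size is illustrative only. It is about 0.1 to 0.4 points on fine motor (7% to 26% of the target difference) if 15% of children are affected, they score 0.5 to 1.0 SD lower, and 10% are removed in one arm against 5% or 0% in the other. It is nil if similar children are removed equally. The change is worth making because it costs almost nothing and closes off an avoidable risk.

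**What to change.** Replace 'or later' with a cut-off at the baseline measurement, that is, at transfer from Phase I to the Transition Phase, and apply it in the same way in both arms. State that a child diagnosed after that point stays in follow-up and in the primary analysis, in the arm of the child's cluster. Record the diagnosis and its date, report late diagnoses by arm, and leave these children out at most in a sensitivity analysis.

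This takes a sentence or two in the eligibility and analysis sections, plus a field for the diagnosis and date. The downside is slightly more outcome variability from retaining ill children. The change concerns who is analysed and has no bearing on a child's clinical care.
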